## Abstract

**Background:**

Critical Events in Anaesthetised Kids undergoing Tracheal Intubation (CRICKET) is a prospective, international multicentre observational study with the objective of capturing, assessing, and analysing critical events associated with tracheal intubation in children.

**Methods:**

CRICKET involves paediatric patients aged 0–16 yr, requiring tracheal intubation, performed by the anaesthesia team for procedures or interventions requiring general anaesthesia, either planned or unplanned. Patient characteristics and airway management techniques are recorded using a dedicated electronic case report form. If one or more critical events associated with airway management occur, a second, more detailed questionnaire will be completed for the follow-up until the patient is discharged or up to a maximum of 30 days. We aim to include 105 000 patients from participating centres disseminated worldwide. Every participating centre collects data over a consecutive observational period of 3 months. The primary outcome is the incidence of critical events associated with tracheal intubation in children.

**Results:**

The CRICKET study started in January 2024 and is currently ongoing. By May 2025, around 25 000 patients were entered into the database, with an estimated 50 000 patients by the end of 2025. Because of the observational nature of the study and the extensive international involvement and effort, continuing the study or analysing the existing data will depend on available resources and exact incidence of critical events.

**Clinical trial registration:**

ClinicalTrials.gov (NCT 05804188).

Tracheal intubation-associated events (TIAEs) can lead to immediate life-threatening complications and long-term sequelae, especially for very young patients and those affected by comorbidities.^1^^,^^2^ The fourth National Audit Project (NAP4)^3^ in the UK estimated that major complications during airway management occur with an incidence of up to 1 in 5500 anaesthesia cases in adults and children. In this audit, the few reported cases with a ‘cannot intubate cannot oxygenate’ (CICO) situation had very severe consequences (death, brain damage, prolonged hospitalisation, unplanned ICU admission). The APRICOT study^4^ reported an incidence of difficult airway, defined as Cormack–Lehane (CL) grading of 3 or 4 or three or more attempts to insert the tracheal tube, of 0.9%, increasing in neonates to 5%, with 40% of these patients suffering from hypoxemia and 8% from hypoxemia and bradycardia. Fortunately, only a small number of severe TIAEs led to long-term morbidity or increased mortality. This low rate of serious sequelae mirrors findings from NECTARINE^5^ and PeDI,^1^^,^^6^ and likely reflects the benefits of early recognition and timely intervention.

Infants and children experience a higher rate of airway-related critical events owing to age-dependent anatomical and physiological features, and syndromic conditions and comorbidities. Therefore, they deteriorate rapidly if not expertly managed. Human factors and variable team performance further influence outcomes, underscoring why current guidelines^2^^,^^7^^,^^8^ advocate limiting attempts, seeking help early, and structured debriefing. Despite these recommendations, practice remains heterogeneous. The Critical Events in Anaesthetised Kids undergoing Tracheal Intubation (CRICKET) study is therefore crucial, providing contemporary, real-world data on paediatric airway management, identifying where gaps persist, and defining priorities to enhance safety and reduce preventable harm.

Where earlier studies have reported critical events in broad terms, often limited to severe outcomes such as cardiac arrest or death, the CRICKET study will address this gap by prospectively capturing detailed, standardised data on a vast number of airway-related critical events during tracheal intubation in children up to 16 yr of age. The inclusion of centres with diverse geographic and economic backgrounds enhances the generalisability and external validity of the study's findings.

## Methods

The primary aim is to determine the incidence of paediatric patients presenting with critical events associated with tracheal intubation. Table 1 presents definitions of critical events used in this study. As an observational study, CRICKET remains inherently susceptible to confounding by indication, although its large sample size and detailed, standardised data collection will help to characterise and mitigate this potential bias. Analysis of these events will focus on identifying clusters of events and risk factors for frequently occurring events. For example, in some conditions, critical events might be characterised by two or more airway-related complications occurring in close temporal proximity during the same intubation episode, suggesting a connected cascade (such as desaturation followed by bradycardia and hypotension) rather than isolated, unrelated events. Similarly, clusters of particular events might be identified in a specific subgroup of patients. This may allow us to identify independent risk factors and, consequently, children at particular risk for critical events.

**Table 1 tbl1:** Definition of critical events associated with tracheal intubation. CPAP, continuous positive airway pressure.

Definition of tracheal intubation-associated critical events	
‘Critical events’ in this study and time frame	Any episode of occurrence during tracheal intubation requiring a medical intervention from the start of anaesthesia until the end of anaesthesia (defined as handover to either the PACU, the paediatric or neonatal intensive care unit, the ward, or discharge home straight from anaesthesia care).
Severe hypoxemia	SpO_2_ <85% or >20 points below initial value for at least 60 s.
Severe bradycardia	Persistent bradycardia for at least 1 min: • 0–3 months old: HR <80 beats min^−1^ • 4 months–2 yr: HR <60 beats min^−1^ • 2–10 yr old: HR <40 beats min^−1^ • 10–16 yr old: HR <30 beats min^−1^
Oesophageal intubation	Tracheal tube placed in the oesophagus diagnosed by (video-) laryngoscopy, absence of sustained EtCO_2_ trace, absence of lung ventilation (auscultation or absence of chest excursions) causing a decrease in oxygenation.
Laryngospasm	Complete airway obstruction associated with rigidity of the abdominal and chest walls and leading to unsuccessful child’s ventilation, or glottic closure associated with chest movement but silent unsuccessful child’s respiratory efforts and assisted ventilation, unrelieved in both situations with simple jaw thrust and CPAP manoeuvres and requiring the administration of medication (propofol, suxamethonium etc.), tracheal (re)-intubation, or both.
Bronchospasm	Increased respiratory effort, especially during expiration, and wheeze on auscultation. Episode of bronchospasm requires the administration of a bronchodilator.
Stridor after extubation	Severe inspiratory flow limitation with sternal retraction, intrathoracic pressure swing, and potentially cyanosis occurring after extubation with or without the administration of oxygen; i.v. steroids, epinephrine (nebulisation), or both; or tracheal intubation. This can be documented clinically or with diagnostic examination, with persistence of symptoms.
Obstruction of tracheal tube	Obstruction of tracheal tube needing lavage or tube exchange.
Airway bleeding	Acute bleeding from nose, arytenoids, or pharynx causing obstruction or risk for pulmonary aspiration.
Can’t intubate can’t oxygenate (CICO)	Situation when there is failed intubation and failure to adequately oxygenate using facemask ventilation or supraglottic airway device resulting in increasing hypoxemia in an anaesthetised and paralyses patient.
Severe bradycardia/cardiac arrest	Cessation of circulation (no pulse) or severe bradycardia requiring chest compressions, during the intubation/extubation manoeuvres.
Pulmonary aspiration	Presence of non-respiratory secretions (gastric, particulate, blood) in the airway as evidenced by (video-)laryngoscopy, suctioning, or bronchoscopy or radiologic signs.
Pneumothorax/pneumomediastinum	Air in the thorax, mediastinum, or both as a consequence of tracheal intubation and ventilation, causing lung collapse or mediastinum dislodgment diagnosed by lung ultrasound, X-ray, or both.
Negative pulmonary oedema	Non-cardiogenic pulmonary oedema that results from the generation of high negative intrathoracic pressure needed to overcome upper airway obstruction.

In accordance with Pediatric Advanced Life Support (PALS) guidance,^9^ bradycardia will be defined as a sustained age-specific slow heart rate with clinical compromise and differentiated from tachyarrhythmias or rhythm disturbances that may also cause haemodynamic instability, but require substantially different treatments. Tachyarrhythmias will be recorded separately, if they occur, as critical events during airway management.

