### Outcome measurements

#### Primary outcomes

The primary study outcome is the incidence of anaesthesia cases with critical events (definitions in Table 1) associated with airway management requiring tracheal intubation, from the start of anaesthesia until the discharge of the patient from the PACU or end of anaesthesia (defined as handover to the paediatric or neonatal intensive care unit, the ward, or discharge home straight from anaesthesia care) in children aged 0–16 yr.

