### Study population and eligibility criteria

Patients are eligible if they fit the following inclusion criteria:•All paediatric patients, aged 0–16 yr, requiring tracheal intubation, either planned or unplanned, performed by the anaesthesia team for procedures or interventions requiring general anaesthesia.•Cases in which a surgeon performs the intubation, whether electively or as a rescue, will be included. Likewise, patients who already have an airway in place (e.g. tracheostomy or tracheal tube) and subsequently undergo airway removal followed by a new intubation will also be captured.

Exclusion criteria are as follows:•Patients >16 yr.•Patients admitted to the operating room already intubated and not requiring a tube exchange.•Refusal to give consent or withdrawal of consent if such is required by the relevant ethics committee.

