### Statistical analysis

A descriptive analysis of the data will be carried out, using counts and percentages to summarise categorical data and median (interquartile range) to summarise continuous data.

The incidence of critical events will be estimated and reported together with a 95% confidence interval. Furthermore, critical event incidence will be provided for different age categories, operator’s experience, operator’s speciality, and centre volume.

In terms of risk factor analysis, a univariable and multivariable mixed-effect logistic regression model will be computed based on possible predictors, which include for example age (≤12 months), weight (≤10 kg), number of attempts (more than two), presence of comorbidities (ASA score ≥3), comorbidity related to airway management (e.g. relevant syndromes), expected difficult intubation, type of anaesthesia induction (i.v. or inhalation), no neuromuscular blocking agent given, airway surgery or ears, nose, throat (ENT) surgery, and experience level of the person performing tracheal intubation. Appendix 1 lists the relevant factors used for primary and secondary analyses. Goodness-of-fit, calibration, discriminatory capacity, and predictive skill of the regression models will be assessed using Nagelkerke pseudo-*R*^2^, calibration belts, area under the receiver operating characteristic curve (AUROC), and Brier Score, respectively.

The target sample size for CRICKET is informed by statistical considerations and the practical constraints of conducting a large, multinational observational study. Although the sample size calculation indicates that approximately 105 000 cases are required to estimate an event rate of 0.5–1% with acceptable precision, the achievable enrolment also depends on centre capacity, case volume, and the coordinated activation of participating sites across multiple jurisdictions. Recruitment will therefore proceed sequentially from January 2024 to December 2025, with each centre contributing a consecutive 3-month sampling window once local approvals and resources are in place. If the required sample size is not reached by the end of 2025, the steering committee may extend the recruitment period or, alternatively, close enrolment and proceed with analysis of the accrued data, depending on the number of events captured and the resources remaining.

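### As worded, the initial-value limit in the severe-hypoxaemia definition can never operate, so a child who starts below 85% meets the numerical threshold without deteriorating

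*Protocol article*

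**What the plan says.** In the Protocol article, Methods, Table 1, severe hypoxaemia is "SpO_2_ <85% or >20 points below initial value for at least 60 s". The first row of that table sets a condition on every event: "Any episode of occurrence during tracheal intubation requiring a medical intervention from the start of anaesthesia until the end of anaesthesia".

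Under Primary outcomes, the trial estimates the "incidence of anaesthesia cases with critical events (definitions in Table 1) associated with airway management requiring tracheal intubation". A case whose only event is severe hypoxaemia therefore counts.

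Under Study population and eligibility criteria, the study takes "All paediatric patients, aged 0–16 yr, requiring tracheal intubation, either planned or unplanned". The exclusions concern age, a tube already in place that needs no exchange, and consent. None concerns a low starting saturation.

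Under Assessments of outcomes for data quality, an event exists only if the treating anaesthesia provider affirms it. The Clinical Event Committee (CEC) reviews all reported events and may change their type or severity, but it may not reverse a clinician's confirmation. The Statistical analysis section lists ASA score 3 or more among the candidate predictors.

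**The concern.** A limit stated relative to the initial value shows that the authors thought baseline saturation mattered. It matters most for children who start low. Joined by 'or' to an absolute limit of 85%, however, the relative limit cannot do anything for them: the absolute limit has already classified them, whether or not anything happened during intubation.

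Other rows of Table 1 do require a change. Oesophageal intubation must cause oxygenation to fall, and the can't-intubate-can't-oxygenate row refers to worsening hypoxaemia. The severe-hypoxaemia row requires no change from a child who starts below 85%.

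At stake is the primary numerator. If some centres apply the numbers literally and others use judgement, the same stable child is classified differently. Any misclassification would fall on children with a low baseline. If they are mostly children with comorbidity, it would also enter the risk-factor model. A larger sample does not remove an error of this kind.

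**Working it through.** **Planned precision (the plan's own figures).** Sample size calculation states a target interval of 0.9–1.1% around 1%, a half-width of 0.1 percentage point. Its conservative scenario is 0.5% with a half-width of 8.5% of the rate, that is 0.085 × 0.5% = 0.0425 point. The Wilson half-width is z·√(n·p·(1−p) + z²/4) / (n + z²). Solving for n with z = 1.96 gives 105 992 for p = 0.5% (Table 2: 105 897) and 52 727 for p = 1% at 8.5% (Table 2: 52 714). The plan's figures reproduce, and the sample size is not in question here.

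**Step 1: can the second limit add a case?** Let S0 be the initial and S the current saturation. The second limit, ">20 points below initial value", requires S < S0 − 20. Since S0 ≤ 100, this gives S < 80, which already satisfies S < 85. An enumeration of all pairs from 0 to 100% in 0.1-point steps found 0 pairs that meet the second limit but not the first. It also found 0 when the fall is read as 20% of the initial value.

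**Step 2: does the duration rescue it?** The words "for at least 60 s" appear once, at the end of the row.

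| Reading of the 60 s | Cases added by the second limit |
|---|---|
| governs both limits | none |
| governs the second limit only | none; any momentary value below 85% then counts |
| governs the first limit only | brief falls of more than 20 points |

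Only the third reading makes the second limit work, and the word order does not support it.

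**Step 3: what happens at a low baseline?**

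| Initial SpO2 | Fall needed for the first limit | Second limit alone would require |
|---|---|---|
| 75% | none | below 55% |
| 80% | none | below 60% |
| 84% | none | below 64% |
| 95% | more than 10 points | below 75% |
| 100% | more than 15 points | below 80% |

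**Step 4: possible size.** The documents give no share of children with initial SpO2 below 85%. Let f be an assumed share, p the true incidence (taken to be the same in these children), and suppose that every one of them is recorded as an event. The observed incidence is then p + f(1 − p).

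| Assumed f | True 1.00% observed as | True 0.50% observed as |
|---|---|---|
| 0.05% | 1.05% | 0.55% |
| 0.1% | 1.10% | 0.60% |
| 0.5% | 1.50% | 1.00% |

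For f = 0.1% and p = 1%, the shift is 0.1 × 0.99 = 0.099 point, against a planned half-width of 0.1 point. For f = 0.05% and p = 0.5%, it is 0.05 × 0.995 = 0.050 point, against 0.0425 point. These are upper bounds. If only one such child in ten were recorded, the shift would be one tenth as large: about 0.01 point for f = 0.1% and p = 1%.

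**The case against.** A reader might infer that a child with a habitual SpO2 below 85% meets the primary outcome at baseline. The documents do not support that. The general row of Table 1 requires an episode during intubation that needs a medical intervention, Primary outcomes requires an association with airway management, and the provider must affirm the event. Events are not computed from saturation values, and an unchanged chronic value is hard to read as an episode needing intervention. It would also be wrong to say that the intervention clause screens out nobody because every child receives oxygen and ventilation. On that reading the clause would be empty for every event in the table. All of this stands, and it makes full misclassification an extreme assumption.

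The safeguards are still incomplete. The rows for laryngospasm, bronchospasm and tube obstruction name their intervention, whereas the hypoxaemia row gives only numbers. The CEC can reclassify against the protocol definitions, but a child with a low baseline already meets the printed one, and the CEC cannot reverse a confirmation.

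Three further points have force. Hypoxaemia is one of 13 event rows, and the problem may be rare. The full protocol, which is not shown, may give sites guidance, although the printed wording would still be wrong. Data have also been collected under this wording since January 2024, so replacing the definition now would be a post hoc change to the primary outcome.

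**Conclusion.** It is certain from the wording alone that the initial-value limit is inoperative, and that a child starting below 85% meets the hypoxaemia threshold without any fall. No eligibility criterion or other rule in the article deals with such a child, so counting depends on a general clause and individual judgement.

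The effect on incidence cannot be derived from the documents. The figure of about 1.10% for a true 1.00% rests on an assumed 0.1% share and complete misclassification, and shows only that a small share could use up the planned precision. A reader might also infer that the odds ratios for comorbidity or young age are inflated. The documents give no joint distribution of baseline saturation with ASA score or age, and no such effect was calculated. The supportable statement is that part of any association with ASA score 3 or more could be definitional.

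This is a should-fix point: a stated rule within the primary outcome does not work as written, the consequence is of unknown size, and the remedy is cheap.

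**What to change.** Before database lock:

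1. Correct the Table 1 row so that the initial-value limit operates for children whose initial SpO2 is below 85%, requiring a fall from the initial value for them. The exact rule is for the sponsor to set, and it should avoid a step at 85%. Simply switching limits at 85% would count a drift from 86% to 84% (2 points) but not a fall from 84% to 65% (19 points).
2. State which limit the 60 s governs.
3. Keep the printed wording visible, because the data were collected under it. Report the primary incidence and the risk-factor model twice: once under the printed wording, and once with cases whose only event is hypoxaemia, in children with initial SpO2 below 85%, counted only if the initial-value limit is met. The second analysis has the same step at 85%, so it is a sensitivity analysis and not a silent replacement. Done at the analysis stage, it reverses no clinician's confirmation.
4. State for how many of these cases initial and lowest SpO2 were recorded. The article does not say whether the case report form holds both values, and the second analysis is possible only where it does.

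The cost is one clarified row, one derivation and one additional analysis, and possibly a slightly lower incidence in the second analysis.

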### Study design

CRICKET is a prospective, international, multicentre observational study collecting health-related data over a consecutive 3-month period. Centre recruitment will be sequential between January 2024 and December 2025, with each site initiating its observation window upon ethics approval and confirmation of adequate local resources. During the study period, designated research staff or the anaesthetist in charge of the patient will complete a dedicated case report form (CRF) for every child undergoing general anaesthesia with tracheal intubation, whether elective or unplanned. Importantly, CRF data are collected exclusively for research purposes and are entirely separate from the medical record. For cases without critical events, data collection ends at anaesthesia completion and tracheal extubation. When one or more critical events occur, an additional detailed section of the CRF and a structured 24-h follow-up will be completed to document management and possible sequelae. To minimise reporting bias and alleviate concerns about disclosure, data are recorded anonymously, no identifiable staff information is collected, participating centres are not benchmarked against each other, and the study explicitly adopts a quality-improvement-oriented framework to encourage accurate and complete reporting. Any missing data will be actively queried by the local study team to ensure completeness, and variables that remain unresolved after these efforts will be handled using predefined statistical procedures appropriate for observational datasets, including sensitivity analyses and multiple imputations to assess the impact of missingness.

The collected health-related data will be entered into an electronic research database in REDCap® (Vanderbilt University Medical Center, [name]) (Research Electronic Data Capture)^10^, ^11^, ^12^, ^13^, ^14^, ^15^ (see Data Management section). In this database, data will be encoded to ensure that neither patients nor providers are identifiable. The study flowchart is presented in Figure 1.

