## Discussion

### Assessments of outcomes for data quality

For every patient, the anaesthesia provider will complete an electronic questionnaire in REDCap®, together with an expanded form whenever a critical event related to tracheal intubation occurs. Because complications may arise at any time during anaesthesia, treating clinicians act as an extension of the study team and are responsible for real-time, case-specific data entry; however, these study forms remain entirely separate from the clinical record. To ensure completeness and minimise reporting bias, dedicated research staff, when available and not involved in clinical care, will perform daily checks of all cases from the preceding 24 h, reviewing submitted questionnaires for clarity and retrieving missing information. Where clarification is needed, queries may be returned to the individual clinician who performed the case, ideally close to end of the case and without collecting any identifiable information. Study personnel will not infer the occurrence of a critical event solely from the medical record: an event must be affirmatively documented by the treating anaesthesia provider. Conversely, the independent Clinical Event Committee (CEC) will adjudicate all reported events, ensuring consistency with study definitions and assigning severity levels; however, the CEC cannot overrule a clinician’s explicit confirmation that an event occurred, although it may reclassify the event type or severity based on the protocol definitions. Data quality verification will take place only after all ancillary datasets are merged into the main REDCap® database. Once all outstanding queries are resolved and data quality procedures completed, the database will be locked for statistical analysis.

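### Operator experience is analysed as a risk factor but no operator code is described; if none is kept, its model-based intervals ignore differences between operators within a centre

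*Protocol article*

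**What the plan says.** On data capture, the Study design section states that "data are recorded anonymously, no identifiable staff information is collected", and that in the database "data will be encoded to ensure that neither patients nor providers are identifiable". The section on assessments of outcomes for data quality adds that "queries may be returned to the individual clinician who performed the case", so a site can trace a case to its clinician. The article does not say that this trace enters the database in coded form.

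On analysis, the Statistical analysis section states that "a univariable and multivariable mixed-effect logistic regression model will be computed based on possible predictors". One of the listed predictors is the "experience level of the person performing tracheal intubation". The same section also plans descriptive results by operator: "critical event incidence will be provided for different age categories, operator’s experience, operator’s speciality, and centre volume". The level of the random effect (centre, operator or child) is not named, and neither is the variance estimator.

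**The concern.** Experience and speciality are attributes of the operator. One operator may intubate many children in a 3-month window, and all those cases share that person's own tendency to have events. The information about experience therefore depends partly on how many operators there are, not only on how many cases.

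A centre random intercept does not deal with this. Junior and senior operators work side by side, so their comparison is largely made within centres, and differences between operators in the same centre remain after the centre effect is removed. A model-based standard error then treats those cases as independent given the centre and is too small for an operator-level factor.

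At stake are intervals for experience that look more certain than they are, and chance differences reported as risk factors more often than the nominal rate. The stated data-collection choice bears directly on the stated analysis. The Results section says recruitment stops at the end of 2025, so if no code was captured, the remedy has to come from the analysis.

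**Working it through.** **1. The plan's own figure.** The sample size solves the Wilson half-width for n:

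d = z·√(pq/n + z²/(4n²)) / (1 + z²/n)

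With p = 0.005, d = 0.085 × 0.005 = 0.000425 and 95% confidence, n = 105 992. Table 2 states 105 897, a difference of 95 (0.09%). The other seven cells also agree within 0.1%. The planning therefore treats cases as independent with no design effect. The article gives no intracluster correlation, number of operators or cases per operator, so everything below rests on assumptions.

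**2. Formula for an operator-level factor.** With m cases per operator and correlation ρ between cases of one operator, the true standard error exceeds the independence one by

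F = √(1 + (m − 1)ρ), and the understatement is 1 − 1/F.

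Here ρ = Var(q)/[p(1 − p)], where q is the operator's own event probability under a normal operator effect on the log-odds scale. With m = 30 (assumed):

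| Event rate | Operator SD | ρ | 1 + 29ρ | F | SE understated by |
|---|---|---|---|---|---|
| 0.5% | 0.5 | 0.0014 | 1.041 | 1.020 | 2.0% |
| 0.5% | 0.7 | 0.0031 | 1.090 | 1.044 | 4.2% |
| 1% | 0.5 | 0.00276 | 1.080 | 1.039 | 3.8% |
| 1% | 0.7 | 0.00612 | 1.177 | 1.085 | 7.8% |
| 6% | 0.5 | 0.01496 | 1.434 | 1.197 | 16.5% |
| 6% | 0.7 | 0.03077 | 1.892 | 1.376 | 27.3% |

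Over a wider range (SD 0.3 to 1.0), F at 1% runs from 1.00 to 1.07 with 10 cases per operator and from 1.02 to 1.32 with 50. At 6% the ranges are 1.02 to 1.26 and 1.12 to 2.06.

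**3. Simulation.** Assumed: 200 centres, 8 operators each, about 30 cases per operator (200 × 8 × 30 = 48 000 cases), half the operators junior, centre SD 0.5, true odds ratio 1, 1500 data sets per setting. The estimator was a centre-stratified Mantel-Haenszel odds ratio, a stand-in for the planned multivariable model. The simulation was run twice, the 0.5% setting once. Rejection rates at nominal 5% using the independence variance:

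| Event rate | Operator SD 0.5 | Operator SD 0.8 |
|---|---|---|
| 0.5% | 5.5% | 5.6% |
| 1% | 6.4% and 7.2% | 9.1% and 9.8% |
| 3% | 8.2% and 8.2% | 15.0% and 17.6% |
| 6% | 11.3% and 11.1% | 21.1% and 20.1% |

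The Monte Carlo error near 5% is √(0.05 × 0.95/1500) = 0.6 percentage points. Standard errors clustered on the centre gave 4.4% to 6.7% across settings. With operator SD 0 the independence variance held 5% to 6%, so the excess comes from the operators. For SD 0.5 to 0.8 the simulated standard error was understated by about 6% to 15% at a 1% rate and 19% to 36% at 6%.

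**4. Combined range.** At 1%, the formula's lower end and the simulation's upper end give roughly 4% to 15%. At 6%, the simulation gives about 20% to 35%; the formula's lower end, at SD 0.5, is slightly less.

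**5. Repeat cases in one child.** If a share f of children have two cases, the mean cluster size is 1 + f and the mean squared size is 1 + 3f. For the most extreme values tried, f = 0.10 and ρ = 0.3: F = √(1 + (1.3/1.1 − 1) × 0.3) = √1.0545 = 1.027. The effect is below 3%.

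**The case against.** The strongest objection is that the article proves neither premise. It excludes identifiable staff information; it does not say that no operator link exists, and a pseudonymous code fits encoded data. It plans a mixed-effect model without naming the grouping, so an operator level may already be intended. Random-effect structure and variance estimator are commonly left to an analysis plan, which is not shown. This stands: a reader might infer that cases by one operator cannot be linked, or that the intervals are certainly too narrow, and the documents support neither. The point holds only conditionally.

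The size is also open to challenge. Every clustering input is assumed, the effect is negligible at 0.5%, and at 1% with SD 0.5 the excess over 5% is small against simulation error. The 20% rejection rates need both the top of the 0.28% to 6% range cited in the sample size section and the larger SD. This stands too. Against it, the 0.5% to 1% planning rates are described as conservative and refer to the less represented age groups, so the overall rate of the broad composite in Table 1 could be higher.

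Two wider readings fail. A reader might extend the point to children anaesthetised more than once, since the aim is to "determine the incidence of paediatric patients presenting with critical events associated with tracheal intubation" while "The primary study outcome is the incidence of anaesthesia cases with critical events". The two units do differ, but the effect on standard errors stayed below 3% in every scenario tried. A reader might also extend it to the overall incidence or to all risk factors. The calculations here cover only factors that belong to the operator; age, weight, ASA score and induction type vary from case to case.

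What remains is that a stated capture rule may prevent an operator level in a model that estimates an operator attribute, and that the remedy works whether or not a code exists.

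**Conclusion.** The point holds conditionally. If no non-identifying operator code is kept, the mixed-effect model can carry at most a centre effect, and model-based intervals for operator experience, and for any estimate by speciality, are too narrow to the extent that operators within a centre differ.

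With 8 operators per centre, about 30 cases each and an operator SD of 0.5 to 0.8, the effect is negligible at a 0.5% event rate. The standard error is understated by roughly 4% to 15% at 1% and by about 20% to 35% at 6%. None of these clustering inputs is in the documents. The primary incidence is outside this point. It is a worthwhile, inexpensive improvement to a secondary analysis, not a demonstrated error.

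**What to change.** In the Statistical analysis section, state that odds ratios for operator-level factors (experience, and speciality if it is modelled) are reported with standard errors clustered on the whole centre, by a sandwich estimator or a whole-centre bootstrap. Provided each operator works in one centre only, this allows for operator differences without any identifier.

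State also whether the database holds a non-identifying operator code. If it does, an operator random intercept nested in centre is the alternative.

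The cost is a sentence of text and a standard software option. No new data are needed and the promised anonymity is kept. The downside is slightly wider intervals for these factors.
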